## Methods

### Study Oversight and Schedule

Projecte Moviment is a multi-center, single-blind randomized controlled trial that started November 2015 with the aim of recruiting 140 participants distributed in four parallel groups (one control group, *n* = 20; three intervention groups, *n* = 40 each). All participants give their written informed consent and are assessed at baseline and 3 months later, immediately after the intervention (Figure 1). This study is led by the Faculty of Psychology of the University of Barcelona in collaboration with Institut Universitari d’Investigació en Atenció Primària Jordi Gol, Hospital Germans Trias i Pujol and Institute Guttmann; it was approved by the responsible ethics committees following the Declaration of Helsinki.

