Mini-Mental State Examination (MMSE)		X								X	
Geriatric Depression Scale (GDS-15)		X								X	
Medical history			X								
General health status			X						X		
Blood extraction			X						X		
Battery of neuropsychological tests				X						X^1^	
Psychological health and daily activities scales				X						X	
Physical activity questionnaire (VREM)				X						X	
Cardiorespiratory fitness (Rockport 1-mile walk test)				X						X	
Magnetic resonance imaging					X						X
Information about intervention						X					
Follow-up adherence questions^2^							X	X			
Actimeter^3^ (Polar Loop^®^)						X		X			
Intervention follow-up diary^4^						X	X	X			

*^1^All of tests except vocabulary subtest; ^2^This information is also collected in phone calls every 2 weeks between visits; ^3^Participants carry the actimeter the first and last week of training; ^4^Participants record the diary every day during the intervention; MoCA 5-min (Wong et al., 2015); MMSE (Blesa et al., 2001); GDS-15 (Martínez et al., 2002); VREM – Reduced Minnesota leisure time physical activity questionnaire (Ruiz et al., 2012); Rockport 1-mile walk test (Kline et al., 1987).*

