### Analyses

#### Power Analysis

The sample size was determined considering previous studies (Erickson et al., 2011) and the effect size and the standard error of cardiovascular interventions on all cognitive tasks reported in a previous meta-analytic study (Colcombe and Kramer, 2003). We also considered the following assumptions: bilateral contrasts and an effect size of 0.4 using the Tukey–Kramer multiple comparison test at 0.05 significance level with a common standard deviation within a group of 0.3. In order to have at least 80% statistical power to answer the 3 primary aims of the project, we need 18 subjects in the control group and 36 for CCT, AE, and COMB groups, respectively. Assuming 10% of lost to follow up (Rahe et al., 2015), we need a total sample size of 139 subjects (control group *n* = 19, intervention groups *n* = 40). Sample power has been computed using PASS 14 Power Analysis and Sample Size Software.

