#### Statistical Analyses

Addressing the primary objective, statistical procedures will be performed with IBM SPSS Statistics 24 and R Environment. The distribution of raw scores will be examined in order to assess data quality (i.e., outliers, skewness) and we will obtain sample *z*-scores for all cognitive tests. Five primary domains will be calculated by adding *z*-scores – executive function, memory, language, attention-speed, and visuospatial function – which will be split into nine secondary domains in order to assess specific changes within each domain – inhibition, fluency, working memory, verbal memory, visual memory, language, attention, speed and visuospatial function (see Table 3). Domains will be based on the literature (Strauss and Spreen, 1998; Lezak et al., 2012) given the fact that a principle component analysis would not be appropriate for our sample size.

In order to test our primary hypotheses, we will conduct an intention-to-treat (ITT) analysis considering data from all randomized participants, including those that complete and drop-out, in order to prevent attrition bias. An adequate method of imputation will be applied and informed. Parametric or non-parametric tests will be chosen regarding the fitting of data to statistical requirements of the tests and we will follow a coherent pipeline to explore variance: (a) comparison of baseline values between groups to identify potential variables to adjust further analyses; (b) comparison of variables at different time-points for each group to identify the independent effect of each condition; (c) identification of significant cross-time correlations in order to determine whether it is necessary to control for baseline measures; (d) interaction between conditions and time-points to compare interventions. Sex, age, and years of education will be considered covariates beforehand and a two-tailed *p*-value < 0.05 will be set as the significant threshold and the corresponding correction for multiple comparisons will be applied. In a second phase, we will define a per-protocol (PP) sample including only subjects that finished the intervention with at least 80% adherence and we will reproduce the same pipeline. In case of high disparity between ITT and PP results, we will analyze potential variables related to that discrepancy.

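### Step (c) lets a significance test on the trial's own data decide whether each primary outcome is adjusted for baseline; the baseline value should be a fixed covariate

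*Protocol article*

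**What the plan says.** The Statistical Analyses section of the protocol article sets out a four-step pipeline for the primary hypotheses.

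- Step (a): "comparison of baseline values between groups to identify potential variables to adjust further analyses". No test or threshold is named in this step.
- Step (c): "identification of significant cross-time correlations in order to determine whether it is necessary to control for baseline measures".
- Step (d): "interaction between conditions and time-points to compare interventions".
- Fixed covariates: "Sex, age, and years of education will be considered covariates beforehand". The baseline score of the outcome is not among them.
- Threshold: "a two-tailed *p*-value < 0.05 will be set as the significant threshold", with a correction for multiple comparisons.

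The pipeline is repeated in the per-protocol sample and is used there for the secondary hypotheses too. The baseline values exist: under Study Oversight and Schedule, participants "are assessed at baseline and 3 months later, immediately after the intervention". The one exception is a footnote to Table 2, which gives the follow-up battery as "All of tests except vocabulary subtest".

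**The concern.** Whether an outcome is adjusted for its baseline should be settled before the data are seen, on the ground that baseline predicts follow-up. Step (c) replaces that with a significance test, whose result depends on sample size and noise as well as on the correlation. Three things follow.

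- The estimator is not fixed. One domain may be analysed by ANCOVA and the next by change score. The same domain may switch between the intention-to-treat and per-protocol runs, and the plan intends to examine disparities between those runs. Part of such a disparity could come from the switch of model.
- The rule is incomplete. It does not say whether the correlation is taken per arm or over all participants, or what happens if arms disagree.
- With two time points, the unadjusted condition-by-time interaction in step (d) is a comparison of change scores. That is less precise than ANCOVA at every correlation below 1, and it carries chance baseline imbalance into the result through regression to the mean.

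**Working it through.** **Inputs.** From Power Analysis: 18 evaluable controls and 36 per intervention arm, so 18 + 3 × 36 = 126, with Tukey–Kramer at two-sided 0.05. The documents give no baseline–follow-up correlation (rho). I assume 0.3, 0.5 and 0.7 as the main range.

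**The plan's own figure.** The Tukey critical value for 4 groups and 122 df is 2.605. The standard error of an intervention-versus-control difference, in SD units, is √(1/18 + 1/36) = 0.289. Taking the stated difference of 0.4 and SD of 0.3 literally gives 1.33 SD and 97.7% power per comparison, not 80%. A difference of 1.0 SD gives 80.3%. That mismatch is a separate matter. I use 1.0 SD below because it is the difference at which the stated sample size gives the stated power.

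**When step (c) triggers.** The smallest significant correlation is r = t/√(n − 2 + t²):

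- n = 18: 2.120/√(16 + 4.494) = 0.47
- n = 36: 2.032/√(34 + 4.130) = 0.33
- n = 126: 1.979/√(124 + 3.917) = 0.175, about 0.18

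An observed correlation of 0.40 would therefore call for adjustment in an intervention arm and in the pooled sample, but not in the controls.

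**Precision when it does not trigger.** Relative to the follow-up score alone, the variance is 2(1 − rho) for change and 1 − rho² for ANCOVA. Their ratio is (1 + rho)/2.

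| rho | change | ANCOVA | ANCOVA/change |
|---|---|---|---|
| 0.3 | 1.40 | 0.91 | 0.65 |
| 0.5 | 1.00 | 0.75 | 0.75 |
| 0.7 | 0.60 | 0.51 | 0.85 |

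**Power of the rule itself.** I simulated four arms of 18, 36, 36 and 36, with a 1 SD difference and a Tukey critical value. The rule used ANCOVA if the correlation was significant and the change score otherwise (10,000 runs, simulation error about half a percentage point or less).

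| rho | always ANCOVA | rule, pooled over 126 | rule, 18 controls only | always change |
|---|---|---|---|---|
| 0.3 | 84% | 82–83% | 67% | 62% |
| 0.5 | 91% | 91% | 86% | 80% |
| 0.7 | 98% | 98% | 98% | 97% |

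The rule triggers in about 90% or more of pooled samples at rho 0.3 and in practically all of them from 0.5. In the controls alone it triggers in about 23%, 59% and 93%. At rho 0.2 it triggers in about 61% of samples even when pooled over 126.

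A second simulation took only the 18 and 36 people being compared, with a 0.8 SD difference and unadjusted 0.05. Always adjusting against the rule gave 81.0% against 74.6% at rho 0.3, and 78.3% against 64.9% at rho 0.2.

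**Type I error.** In that two-arm setting, step (c) applied mechanically rejects a true null about 5% of the time at nominal 5%.

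**Step (a).** Read as a 0.05 screen, it flags a chance difference in 5% of comparisons under randomisation. For at least one of the five primary domains that is 1 − 0.95⁵ = 23%, if they were independent.

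**The case against.** The strongest reply is that the rule does little harm in practice. Step (d) already uses baseline through the change score, so no analysis ignores it. If cognitive composites correlate well over three months, step (c) will almost always select ANCOVA. At rho 0.7 the rule and the fixed model have the same power, and the same holds at 0.5 if arms are pooled. If the difference really is 0.4 with SD 0.3, power is about 90% or more under either analysis for rho from 0.3 to 0.7. All of this stands. It limits the power loss but does not supply a reason for the rule: where the correlation is high, the rule gains nothing over always adjusting.

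Three stronger readings are tempting, and the documents do not support them.

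- A reader might infer that the false-positive rate is inflated. It is not when the rule is followed as written. Rates of 5.7 to 9.0% arise only if an adjusted and an unadjusted result are both seen and the better one is kept, which the plan does not propose.
- A reader might charge the plan with the whole gap between ANCOVA and the change score at high rho, or between ANCOVA and a follow-up-only analysis. At high rho the rule would choose ANCOVA, and follow-up-only is not the analysis in step (d).
- A reader might treat step (a) as a certain significance screen and count every composite as an independent chance of a false alarm. The step names no test. In Table 3, language and visuospatial function are the same composite at both levels, and the other scores are nested.

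It could also be said that a statistical analysis plan would settle this. But the article states a rule rather than leaving the point open, and a plan that followed the article would inherit it.

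**Conclusion.** The point holds as a pre-specification and efficiency weakness. Step (c) is explicit, the baseline score is absent from the fixed covariates, and nothing elsewhere in the article overrides this. The certain consequence is a primary model that is not fixed and may differ between domains and analysis samples. The power consequence depends on rho and on how the correlation is computed, neither of which the article gives. For a 1 SD difference it ranges from practically nothing at rho 0.7, through one to two percentage points at 0.3 when pooled, to about 17 points at 0.3 when tested in the controls alone (84% − 67%). Step (a) is a weaker part of the case: only if it is read as a p < 0.05 screen does it choose covariates on chance imbalance. The change should be made, but the flaw does not invalidate the trial.

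**What to change.** Drop step (c), and drop step (a) as a way of selecting covariates. Show baseline values descriptively. For each outcome measured at both times, pre-specify one model: follow-up value on arm, with that outcome's own baseline value, sex, age and years of education always included. An equivalent mixed model with baseline means constrained equal across arms would also serve. Use the same model in the intention-to-treat and per-protocol runs.

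WAIS-III Vocabulary has no follow-up value, so the Language composite and the global score need to be built only from tests given at both times.

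The cost is analysis wording and one degree of freedom per outcome. No new data are needed.

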## Aims of the Study

The primary objective of Projecte Moviment is to examine the effect of CCT, AE, or COMB on cognitive outcomes in healthy physically inactive older adults. The primary hypotheses sustaining this goal are:

1.Computerized cognitive training – 5 times per week for 3 months – will improve general cognitive function as well as trained cognitive functions (executive function, processing speed and memory) measured by composite scores using a battery of validated neuropsychological tests at 3 months compared to a control group.2.Aerobic exercise – 5 times per week for 3 months – will improve executive function, attention-processing speed and memory measured by composite scores using a battery of validated neuropsychological tests at 3 months compared to a control group.3.Combined training – 5 times per week for 3 months – will show greater improvements in general cognitive function, executive function, attention-processing speed and memory measured by composite scores using a battery of validated neuropsychological tests at 3 months compared to a control group.

The secondary objectives of Projecte Moviment are: (a) to determine the effects of these interventions on psychological status and subjective performance on daily activities, CRF, brain structure and function and physiological molecular correlates; (b) to identify genetic, demographic, physiological and brain variables that might predict the effect of the intervention; (c) to identify the association between cognitive effects and other psychological, physiological correlates. Specific hypotheses for each objective will be specified in each article when reporting results. General secondary hypotheses include:

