#### Control Group

Participants in the control group are on the waiting list for 3 months and are asked to keep their normal lifestyle. Once the control condition is finished, they have the option to start one of the interventions (CCT, AE, or COMB). Data of this optional activity will not be included in the trial as they are not considered participants during this period.

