## Data Management and Results

### Data Quality

A computerized database is used to collect and organize all data. Data is collected without personal identifying information using a code assigned by the assessor and researchers will only have access to this information in case of an incident. Data from all participants will be collected regardless of whether the participant withdraws from the intervention or not. Assessments, individual reports and databases will be double-checked. We will follow Data Quality Assessment Checklist and Recommended Procedures (DQA; USAID, 2014) that assesses a variety of dimensions as validity, reliability, timeliness, precision and integrity. Regarding interventions parameters, we will assess the coherence between personal diaries, phone-call follow-ups and actimeter. We will analyze if compliance is related to expected physical changes. In addition, if we identify any issues, we will inform and apply any required statistical procedures to control them.

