We will analyze our secondary hypotheses following the same pipeline in the per-protocol sample to guarantee that we will be studying the effects of the intervention on the previously described outcomes. We will examine potential mediator effects through relationships between primary and secondary outcomes accounting for the intervention condition using adequate correlational methods and linear mixed models. Structural neuroimaging data will be first processed studying whole brain, hippocampus and frontal lobe volumes and white matter microstructure. In a second phase, connectivity and white matter lesions will be analyzed. Data will be published in several papers where detailed procedures and software packages will be described.

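### The between-arm secondary hypotheses (1 to 4) have only a per-protocol analysis set, and that set is undefined for the waiting-list control, so the randomised comparison is given up

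*Protocol article*

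**What the plan says.** The Statistical Analyses section uses two analysis sets.

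- **Primary (cognitive) hypotheses:** an "intention-to-treat (ITT) analysis considering data from all randomized participants, including those that complete and drop-out, in order to prevent attrition bias". The same steps are then repeated in a "per-protocol (PP) sample including only subjects that finished the intervention with at least 80% adherence".
- **Secondary hypotheses:** "We will analyze our secondary hypotheses following the same pipeline in the per-protocol sample to guarantee that we will be studying the effects". No intention-to-treat analysis is named for them. The Results part of the abstract agrees: it attaches intention-to-treat to cognitive outcomes only, and the per-protocol sample to predictors and associations.

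Under Aims of the Study, secondary objective (a) is "to determine the effects of these interventions on psychological status and subjective performance on daily activities", together with fitness, brain and molecular outcomes. General secondary hypotheses 1 to 4 are each worded as a comparison with control, or with the cognitive and control conditions.

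Under Control Group: "Participants in the control group are on the waiting list for 3 months and are asked to keep their normal lifestyle". Under Data Quality: "Data from all participants will be collected regardless of whether the participant withdraws from the intervention or not".

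**The concern.** Hypotheses 1 to 4 ask what the interventions do compared with not receiving them. Randomisation answers that question when everyone randomised is compared. Restricting the intervention arms to people who completed at least 80% of a programme of five days a week selects on behaviour after randomisation. People who manage this may differ from the rest in motivation, health or mood, and such traits can bear on the very outcomes at issue. The per-protocol sample therefore does not guarantee that the intervention effect is being studied; it can mix that effect with the characteristics of adherers.

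The protocol adopts intention to treat for the primary hypotheses to prevent attrition bias, then drops that safeguard for the secondary between-arm effects, where the same reasoning applies. Its Discussion warns that demanding home-based programmes may lead to low adherence, so the filter could remove many participants. What is at stake is every claim of an effect on mood, fitness, brain, and inflammation or vascular risk.

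**Working it through.** **Step 1: reading the sections together.** There is no figure in the plan to reproduce.

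- Statistical Analyses sends the secondary hypotheses to the per-protocol sample and nowhere else.
- Membership requires finishing the intervention with at least 80% adherence.
- Controls have no intervention to finish. Read literally, the rule excludes every control or cannot be applied to them. If controls are to be in the analysis at all, they enter by some other rule, so the arms are not selected alike.
- Data are collected after withdrawal from the intervention, so an all-randomised analysis is feasible.

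**Step 2: how large the bias could be (illustration).**

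Inputs from Power Analysis: 18 evaluable controls, 36 evaluable per intervention arm, two-sided 0.05, Tukey–Kramer test.

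Assumptions, not in the article: p, the share of an intervention arm reaching 80% adherence; r, the correlation between adherence and the outcome change; no true effect; all controls kept; outcome in SD units with SD 1; the same p in all three intervention arms.

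Formulas, with φ and Φ the standard normal density and distribution function:

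- Bias = r × φ(z)/p, where z = Φ⁻¹(1 − p).
- Standard error = √(1/(36p) + 1/18).
- Noncentrality = bias / standard error.
- Unadjusted false-positive rate: noncentral t with 36p + 18 − 2 degrees of freedom.
- Tukey-corrected rate: critical value q(0.95; 4 arms)/√2 with 18 + 3 × 36p − 4 degrees of freedom.

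| p | r | φ(z)/p | Bias (SD) | Adherent n | Standard error | Noncentrality | Unadjusted rate | Tukey rate |
|---|---|---|---|---|---|---|---|---|
| 0.8 | 0.2 | 0.350 | 0.07 | 28.8 | 0.300 | 0.23 | 5.6% | 1.2% |
| 0.6 | 0.3 | 0.644 | 0.19 | 21.6 | 0.319 | 0.61 | 9.1% | 2.5% |
| 0.5 | 0.4 | 0.798 | 0.32 | 18.0 | 0.333 | 0.96 | 15.4% | 5.2% |

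With r = 0 the rates are 5% unadjusted and about 1% per contrast with Tukey, so both columns show inflation.

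**Step 3: checks.** A simulation of 20,000 runs at p = 0.7, r = 0.3 gave a mean bias of 0.15 SD and a false-positive rate of 7.5%. The corresponding normal approximation gives 0.15 SD and 7.8%. At p = 0.9, r = 0.2 the bias is only 0.04 SD and the rate about 5%. A negative r gives bias of the same size in the opposite direction.

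**The case against.** The strongest points on the other side are these.

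- **Control membership.** A reader might infer that the article exempts controls from the 80% filter and keeps all who stay. It does not say so. Such a rule may stand in a fuller document. What remains is that the rule as printed cannot be applied to controls, and that no workable version selects them as the other arms are selected.
- **Scope.** A reader might extend the point to all secondary hypotheses. Hypothesis 5 (predictors) and hypothesis 6 (association of changes) are not simple randomised contrasts. The objection stands, and the point is limited to hypotheses 1 to 4.
- **Direction.** A reader might infer bias toward benefit. The article gives no adherence rate and no adherence-outcome correlation. Adherers who start fitter could improve less, and analysing change removes part of any stable difference. The direction is open.
- **Size.** The unadjusted rates are not those of the planned analysis, which includes a correction for multiple comparisons. With Tukey the worst case shown is about 5% per contrast, although that compares with about 1% without bias. Adjustment for sex, age and education would help in part, but it does not measure motivation or health.
- **COMB as the most selected arm.** At 90 minutes daily against 45 this is plausible, but no adherence figure in the article supports it.
- **Already handled.** The planned look at discrepancies between intention-to-treat and per-protocol results belongs to the primary analysis. It does not supply an intention-to-treat result for hypotheses 1 to 4.

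The effect among people who take the programme as intended is a legitimate question, and a per-protocol analysis is reasonable support. The flaw is that it is the only set stated for these effects.

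**Conclusion.** The point holds for secondary hypotheses 1 to 4. Their only stated analysis set conditions on adherence after randomisation and has no defined rule for the control arm. That this gives up the randomised comparison follows from the text without any calculation. Bias is possible but not demonstrated, and the range in the table depends wholly on the assumed p and r; with high adherence and a weak correlation it is small.

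Severity: should be fixed before analysis. It does not threaten the trial's main conclusion, because the primary cognitive hypotheses are analysed in all randomised participants.

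**What to change.** 1. State that the main analysis of secondary hypotheses 1 to 4 is in all randomised participants, by the same steps and the same handling of missing data as the primary analysis.
2. Keep the 80%-adherence sample as a labelled supportive analysis, adjusted for baseline predictors of adherence, and state how control participants qualify for it.
3. Remove the claim that the per-protocol sample guarantees study of the intervention effect.
4. Hypothesis 6, which concerns associations, may stay in the per-protocol sample.

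Cost: a change of wording and one extra set of runs. No new data collection is needed, since follow-up of those who withdraw from the intervention is already planned. Estimated effects may be somewhat smaller, and missing outcomes will still have to be dealt with.

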Systematic reviews and papers cited before, independently of the intervention, reported inconsistencies across results which likely relate to genetic and environmental variables of participants; type, duration and schedule of assessments; type, duration, frequency, intensity and adherence of interventions; as well as methodological issues of the design, such as type of control group and statistical approaches (Kraft, 2012; Young et al., 2015; Gates et al., 2019). These discrepancies challenge a clear theoretical model and lead to different conclusions and the identification of potential moderators even at the systematic and meta-analytic analysis level. These issues highlight the need to better identify not only the cognitive effects of these interventions but also the individual variables that may predict them and the brain changes and physiological molecular correlates that may be mediating any benefits.

Projecte Moviment is a multi-domain randomized trial that addresses the effect of CCT, AE, and COMB on cognition and psychological status in healthy physically inactive older adults compared to a passive control group. We also aim to identify variables that may predict the effects of the intervention and the underlying brain changes and physiological molecular correlates that may mediate the effects. The purpose of this paper is to describe the protocol in accordance with SPIRIT Guidelines.

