1.All intervention conditions will positively impact psychological and subjective daily functional performance assessed by questionnaires compared to controls.2.Aerobic exercise and COMB will similarly increase CRF and energy expenditure in daily activity compared to cognitive and control conditions.3.All intervention conditions will positively impact the structure and function of the brain assessed by whole brain analyses, structures of interest and white matter lesions volume and microstructure, cortical thickness and functional connectivity compared to a control group.4.Aerobic exercise and COMB will improve immunity, reduce inflammation and improve vascular risk factors compared to cognitive and control conditions.5.Individual variables (i.e., sex, age, cognitive baseline, CRF baseline) will predict the effect of the interventions on cognition.6.Changes in cognition will be related to specific changes in secondary outcomes depending on the intervention.

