### Assessments

Potential participants are screened by phone and an on-site personal interview; if eligible, informed written consent is obtained. Assessments are conducted in a clinical environment and organized into three appointments that take place at baseline – within 2 weeks prior to the start of the intervention, and again at 3 months within 2 weeks after the completion of the intervention (Table 2). (1) Medical assessment (30 min): review of medical history and current health status including cardiovascular risk factors and blood extraction between 8 and 9:30 AM following an overnight fast. (2) Cognitive assessment and physical status (2.5 h): administration of a battery of neuropsychological tests, psychological health, subjective performance, daily activities and PA questionnaires and a treadmill fitness test. In order to control the effects of acute exercise, participants are advised not to exercise prior to all appointments and cognitive tests are conducted before the CRF test. (3) Magnetic Resonance Imaging (MRI) scans (45 min): administration of a neuroimaging protocol to acquire structural and functional data of the brain. All assessments are carried out in two primary care centers except MRI scans that are performed in the Hospital Germans Trias i Pujol. All subjects receive an actimeter the first and last week of intervention to track their daily activity and determine if participants meet the intervention protocol. The same team of psychologists, which administers cognitive tests, and nurses, who collect general health data, follow the protocol in all the centers.

**TABLE 2 T2:** Assessments.

	**Enrollment and screening**		**Baseline assessments** **(within 2 weeks prior to the start of the intervention)**			**Intervention**			**Post-intervention assessments** **(within 2 weeks after the completion of the intervention)**		
				
	**Telephone screening**	**Visit 1: Screening**	**Visit 2: Baseline assessment**	**Visit 3: Baseline assessment**	**Visit 4: Baseline assessment**	**Visit 5: Initial intervention**	**Visit 6: Mid-intervention**	**Visit 7: Final intervention**	**Visit 8: Post-intervention assessment**	**Visit 9: Post-intervention assessment**	**Visit 10: Post-intervention assessment**
First review of criteria	X										
Montreal Cognitive Assessment 5-min (MoCA 5-min)	X										
Information of study	X	X									
Exhaustive review of criteria		X									
Informed consent form		X									

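### A marker can be called a mediator on a within-arm association alone, because no rule joins it to the separate test of whether the intervention moved that marker

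*Protocol article*

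**What the plan says.** The Introduction gives the aim of identifying "the underlying brain changes and physiological molecular correlates that may mediate the effects". Under Aims of the Study, secondary hypothesis 6 is worded more cautiously: "Changes in cognition will be related to specific changes in secondary outcomes depending on the intervention".

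The method is in Statistical Analyses: "We will examine potential mediator effects through relationships between primary and secondary outcomes accounting for the intervention condition using adequate correlational methods". The sentence then adds linear mixed models. The sentence before it says that secondary hypotheses follow the primary pipeline, but in the per-protocol sample, which is defined by completion with at least 80% adherence. Step (d) of that pipeline is the condition-by-time interaction. The pipeline also has a multiple-comparison correction and takes sex, age and years of education as covariates.

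On timing, Study Oversight and Schedule says participants "are assessed at baseline and 3 months later, immediately after the intervention", and Assessments places the second wave "again at 3 months within 2 weeks after the completion of the intervention". Table 2 shows no blood, fitness, MRI or cognitive measurement at the mid-intervention visit.

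**The concern.** Mediation is a claim about two links: the randomised arm changes the marker, and that change carries part of the arm's effect on cognition. A marker-cognition relationship with condition held fixed addresses only the second link, and only through differences between people in the same arm. General health, sleep, ageing or state on the test day could produce such differences in arms where the intervention left the marker untouched.

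The plan examines the first link elsewhere but does not make it a condition for the mediator label. Markers that merely vary with cognition could then be published as mechanisms. The scope for this is wide: the cytokine array alone has 105 analytes, and imaging, fitness and other blood measures come on top. Restricting the analysis to adherent participants also weakens the randomised comparison on which the first link depends.

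**Working it through.** The plan gives no figure for this analysis, so there is none to reproduce. The check sets out what each planned test addresses and then sizes the gap.

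**1. What is tested.** Let *a* be the arm effect on the marker and *b* the marker-cognition slope given arm. The mediated effect is *a* × *b*.
- The stated mediator analysis tests *b* = 0.
- Step (d), applied to the marker, tests *a* = 0.
- No stated analysis tests *a* × *b* = 0, and no rule requires both *a* and *b* to be shown.

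If *a* = 0, the mediated effect is zero however large *b* is.

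**2. How often *b* alone is significant when *a* = 0.** Inputs:
- Evaluable participants, from Power Analysis: 18 + 3 × 36 = 126.
- Per-protocol number: not given; 80 to 120 assumed.
- Within-arm correlation ρ between marker change and cognitive change: not given; 0.2 and 0.3 assumed.
- Four arms need three indicators, so the Fisher z term uses n − 3 − 3 = n − 6.
- Two-sided 5% level without multiplicity correction.

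Probability = Φ(atanh(ρ) × √(n − 6) − 1.96), with atanh(0.2) = 0.203 and atanh(0.3) = 0.310.

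| n | √(n − 6) | ρ = 0.2 | ρ = 0.3 |
|---|---|---|---|
| 80 | 8.60 | 0.41 | 0.76 |
| 100 | 9.70 | 0.50 | 0.85 |
| 120 | 10.68 | 0.58 | 0.91 |

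**3. Effect of requiring both links.** With *a* = 0, a 5% test of the arm effect passes 5% of the time. Under a linear model it is close to independent of the test of *b*. The joint rate per arm-versus-control comparison is therefore between 0.05 × 0.41 = 0.02 and 0.05 × 0.91 = 0.05, and it cannot exceed 5% whatever sample *b* is estimated in. If any of the three arms could qualify a marker without correction, the upper bound is 3 × 0.05 × 0.91 = 0.14, so the multiplicity correction still matters.

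**4. What joining the links cannot do.** The product *a* × *b* was simulated for 36 intervention and 18 control participants, 4,000 trials per case, with an assumed arm effect of 0.8 SD on both marker and cognition.

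| Data-generating structure | Mean *ab*, ρ = 0.3 | Both paths significant | Mean *ab*, ρ = 0.5 | Both paths significant |
|---|---|---|---|---|
| Marker drives cognition | 0.239 | 0.46 | 0.395 | 0.75 |
| Cognition drives marker | 0.244 | 0.47 | 0.405 | 0.76 |
| Common cause only | 0.242 | 0.47 | 0.401 | 0.76 |

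The rows agree to within simulation error (expected values 0.8 × 0.3 = 0.24 and 0.8 × 0.5 = 0.40). The product screens out markers that the arm did not move. It does not tell these three structures apart.

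**5. Precision.** With 18 controls and 36 in an arm, the standard error of a standardised arm effect on a marker is √(1/18 + 1/36) = 0.29 SD before baseline adjustment. The 95% half-width is 1.96 × 0.29 = 0.57 SD.

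**The case against.** The strongest reply is that the arm-to-marker link is planned. Secondary hypotheses 2 to 4 concern arm effects on fitness, brain measures, inflammation and vascular risk, and step (d) tests them. A reader might infer that the plan never asks whether the intervention moved the marker. The document does not support that, and what is missing is only the rule that joins the two results.

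It follows that the 41% to 91% range is not the plan's false-mediator rate. It applies only if the investigators disregard their own arm test. It also uses an uncorrected 5% level although the pipeline includes a correction, and it rests on undocumented correlations. All three limits stand.

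A reader might also object that MRI comes at Visit 10, after the cognitive battery at Visit 9. That carries little weight as a separate argument: the baseline order is the same (Visit 4 after Visit 3), both changes span the same three months, and post-intervention blood at Visit 8 precedes cognition. The real limit is that all measures share the same two waves.

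Finally, the wording is hedged, hypothesis 6 and the abstract speak of association, and detailed procedures are left to later papers. Association is indeed supportable. The article nevertheless states a method under the mediator label, and that method targets a different quantity from the stated aim.

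**Conclusion.** The point holds in limited form. As written, the plan allows a marker that the intervention did not move to be called a potential mediator on a within-arm association in a sample selected on adherence. Under the assumed correlations (0.2 to 0.3) and sample sizes (80 to 120), that association alone would be significant 41% to 91% of the time at an uncorrected 5% level with a mediated effect of exactly zero. Requiring the arm effect too reduces this to about 2% to 5% per comparison.

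The missing joining rule does not depend on those assumptions; the size of the illustration does. No primary result is affected. It would go too far to say that the mediation question will be answered wrongly, or that an indirect-effect estimate would settle causation in this design.

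**What to change.** Replace the mediator sentence in Statistical Analyses with an indirect-effect analysis for each arm against control:

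1. Arm effect on the follow-up marker, adjusted for its baseline.
2. Marker effect on follow-up cognition, adjusted for arm, baseline marker, baseline cognition, sex, age and education.
3. The product of the two, with a bootstrap interval.

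Use all randomised participants with data, with the per-protocol sample as a sensitivity analysis. Call a marker a candidate mediator only if the interval, at the level set by the planned multiplicity correction, excludes zero. Report all other change-change relations as associations.

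Add one limitation: because marker and cognition are measured in the same two waves and the marker is not randomised, even a non-zero product cannot exclude reverse causation or marker-outcome confounding.

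The cost is wording and analysis on data already scheduled, with no new visits. The downside is that fewer markers will be labelled mediators, and intervals will be wide with about 18 controls.
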